## Abstract

**Introduction:**

In kidney transplantation, immunosuppressive therapy is essential to control alloimmune reactions, prevent graft rejection and improve patient survival rates. However, commonly used drugs like tacrolimus (TAC) and mycophenolate mofetil (MMF) have a narrow therapeutic window and exhibit significant inter- and intra-individual variability in pharmacokinetics (PK) and dose-response relationships. Recent pilot studies suggest that the gut microbiome may influence this variability.

**Methods and analysis:**

ElucidatiNg Immunosuppressant pharmacokinetic variabilities by investigating Gut Microbiome modulations After kidney transplantation (ENIGMA) is a prospective, low-interventional, naturalistic longitudinal trial designed to identify biomarkers of TAC and MMF PK variability by examining gut microbiome changes and modulations after kidney transplantation and their link with TAC and MMF PK. Biological samples from 50 patients will be collected at nine specific timepoints pre- and post-transplantation using a rich PK and biological sampling strategy. This approach will enable the derivation of PK parameters for the investigated drugs and the creation of a biobank for future hypothesis testing.

**Ethics and dissemination:**

The ENIGMA trial has received ethical approval from the European Medicines Agency (EMA). The reference number of our project is R&D/1325226 and is registered on the Clinical Trial Information System (CTIS) platform with European Union Clinical Trial number 2023–5 08 335-31-00. Results of the trial will be published in scientific journals and presented at different (inter)national conferences.

**Trial registration number:**

2023–5 08 335-31-00 EMA.

STRENGTHS AND LIMITATIONS OF THIS STUDYLongitudinal design enables in-depth analysis of the relationship between inter- and intra-patient variability in tacrolimus (TAC) and mycophenolate mofetil (MMF) pharmacokinetics (PK) and microbiome dynamics.Integration of at-home volumetric absorptive microsampling in a substudy allows for supplementary TAC and MMF PK data collection, enhancing real-world applicability.Collection of both pre- and post-transplantation samples provides a comprehensive view of temporal biological changes.Extensive biobanking ensures a rich repository of biological samples for future translational research.Limited sample size (n=50) may restrict the statistical power and generalisability of findings.

## Introduction

 Kidney transplantation is the main treatment option for chronic end-stage kidney failure if the patient is suitable for surgery.^1^ Thanks to immunosuppressive therapies of increasing efficacy, the survival of grafts has been constantly progressing over the last decades.^2^ However, the long-term survival rates still need to be improved as maximising long-term graft survival will allow to delay the moment patients will need further transplants, thereby reducing the number of patients on waiting lists.^3^ While the incidence of acute rejection episodes has decreased,^4^ long-term immunosuppression complications have become increasingly evident.^5^

One of the main modifiable risk factors in graft survival is the control of immunosuppression.^3 6 7^ Maintenance therapy currently typically consists of a triple-drug regimen including corticosteroids, a calcineurin inhibitor, tacrolimus (TAC), and an anti-metabolite, mycophenolate mofetil (MMF).^8^ Maintaining optimal levels of immunosuppression while avoiding over- and/or under-dosage due to unexplained pharmacokinetic (PK) variability is essential to prevent increased toxicity and allograft rejection.^9 10^ However, TAC and MMF are known narrow therapeutic-toxic margin drugs and exhibit high interindividual and intraindividual dose-response variations. For TAC, this has led to the implementation of therapeutic drug monitoring (TDM) to avoid inadequate drug levels, thereby minimising the risk of rejection and adverse drug reactions.

Although TDM remains central to the management of TAC-based immunosuppression, it is not routinely used for MMF and constitutes a reactive rather than proactive approach, lacking clear guidelines. For TAC, studies have shown that only 18.5%–37.4% of patients achieve therapeutic levels at first steady state,^11^,^13^ prompting researchers to explore new biomarkers of PK variability. Despite over 1000 publications on TAC dosage requirements depending on the *CYP3A* genotype, mainly *CYP3A5*3* and, to a lesser extent *CYP3A4*22,*^14^ the implementation of pre-emptive genotyping and Clinical Pharmacogenetics Implementation Consortium (CPIC) dosing guidelines^15^ is not widespread in transplant centres, likely due to insufficient evidence of benefits on graft and patient outcomes, a lack of strong guidelines and/or cost.^16^ There is a clear need for new PK biomarkers to improve follow-up care for renal transplant patients.

Previous work has allowed understanding a part of the inter-patient variations in terms of dose-response of TAC and mycophenolic acid (MPA), the active metabolite of MMF. The influence of patient’s genetic profile can explain part of the observed PK variability.^17^ For instance, patients presenting different *CYP3A5* phenotypes show an important shift in TAC metabolism which accounts for approximately 50% of the observed dose-requirement variation and has led to the abovementioned CPIC genotype-based dosing guidelines. For MPA, variants in *UGT1A9* and *ABCC2* have been associated with differences in PK parameters without clear pharmacogenetic testing guidelines or interpretation.^9^ Other factors of inter-patient variations include age at transplantation, co-medications, body surface area and others.^9 17^ More recently, the gut microbiota composition has been shown to be an important factor of inter-individual PK variability.

The importance of the gut microbiome for explaining the fate of immunosuppressive drugs in the organism has been largely understudied although it is now widely accepted that the complex ecosystem of intestinal microbes dynamically takes part in several functions of the host beyond digestion, including drug metabolism.^18^,^22^ Indeed, the gut microbiota synthesises numerous compounds that may interact with and affect the human host metabolome. Not only gut microorganisms express numerous enzymes able to directly metabolise xenobiotics^23^ but they are also able to control the host PK phenotype through different undirect processes.^24^ Inter-individual differences in PK profiles might thus be explained by between-subject differential microbiota composition or function. Moreover, contrarily to the host genetic make-up, the microbiota is not inflexible and might thus be a source of intra-individual variability. Microbiota composition is in fact affected by many environmental factors such as diet, lifestyle, age, physiological status and pharmaceuticals.^25 26^ Studies have highlighted differences in gut microbiota composition of transplanted patients compared with healthy patients,^27^,^29^ with significant changes also observed in the microbiome of patients’ pre-transplantation samples compared with post-transplantation samples,^30^,^32^ indicating a potential interplay between microbiota, transplant status and immunosuppressive pharmacotherapy.

The investigation into the role of the gut microbiome in TAC PK has commenced, with various in vitro and in vivo studies yielding interesting insights. In vitro, Guo *et al* suggest that *F. prausnitzii* metabolises TAC into a less potent immunosuppressive metabolite.^33^ Preclinical results in mice show that microbiota depletion increases *Abcb1a* intestinal expression, leading to a decreased TAC absorption. Additionally, repeated TAC administration also significantly alters gut microbiota composition at various taxonomic levels.^34^ In clinics, gut microbiota composition of TAC-treated renal transplant patients has been associated with different dose requirements in CYP3A5 poor metabolisers.^35^ This effect may be due to the influence of the gut microbiota on the activity of genes important in TAC PK (eg, *ABCB1*). Conversely, gut microbiota might be affected differently by escalating TAC dose.^36^

The gut microbiome is implicated in MPA metabolism, as MPA undergoes enterohepatic recirculation where its inactive metabolite, MPA 7-O-glucuronide, is hydrolysed by bacterial β-glucuronidases to regenerate MPA. MMF has been reported to alter the composition of the gut microbiota by selecting for bacteria expressing β-glucuronidase leading to an upregulation of β-glucuronidase activity in the gut of mice and patients presenting gastrointestinal (GI) side effects.^37^ Additionally, it has been shown that vancomycin eliminated β-glucuronidase expressing bacteria and prevented MMF GI toxicity in mice.^37^ In the same line, another study showed that an intact gut microbiota is required to initiate and sustain the MMF GI toxicity.^38^ From a PK point of view, studies in healthy volunteers treated with cholestyramine have demonstrated that the interruption of the enterohepatic recirculation decreases MPA exposure by approximately 40%.^39^ Furthermore, it has been shown that the inhibition of ABCC2-mediated hepatic excretion paradoxically decreases MPA exposure.^40^ ABC transporter expression modulation by the gut microbiota might be another source of MPA(G) PK variability.

Given the evident interaction between immunosuppressive drugs and the gut microbiome, other medications that affect the gut microbiota may indirectly influence the PK of these drugs. Antibiotics, in particular, have a significant impact on the gut microbiota.^41^ Additionally, transplant recipients are likely to use these drugs due to infections resulting from their compromised immune system.

Immunosuppressant PK variability continues to challenge optimal treatment response in kidney transplant patients. Graft survival and drug-related toxicities remain common clinical issues. Understanding the factors behind treatment response variability is crucial for individualised treatment strategy. Building on previous studies that have shown a connection between the gut microbiome and the response to immunosuppressive therapy in kidney transplant patients, the next step is to explore and characterise how the gut microbiome affects the PK of the two most commonly used immunosuppressive drugs in these patients, with the aim of identifying new biomarkers.

## Hypothesis and objectives

The hypothesis of the trial is that the gut microbiota composition, by inducing physiological changes, is influencing both the oral absorption of TAC and the entero-hepatic recirculation of MPA, thereby impacting on their PK profile, and possibly explaining the variability in the treatment response.

The primary aim of the ENIGMA trial is to identify staging biomarkers of TAC and MMF PK variability by investigating the gut microbiota modulations and physiological changes following kidney transplantation. Additionally, the trial seeks to link PK variabilities, microbiome changes overtime (metabolic and compositional) and responses to immunosuppressive therapy (such as graft survival/rejection and drug-related toxicities). Given the common use of antibiotics in this population, the study will also assess the effect of antibiotherapy interventions on the microbiota composition and the subsequent consequences on immunosuppression pharmacotherapy.

As a secondary endpoint, the study will also explore whether the genotype of the donor and the recipient can predict PK variabilities. Furthermore, it will analyse the response to therapy and related physiological changes from a molecular perspective (ie, transcriptomics, metabolomics and proteomics). Ultimately, this trial aims to link gut microbiota changes and PK variabilities to other blood and urinary-omics data to evaluate their potential as biomarkers and elucidate the underlying mechanisms of the arising observations.

## Method and analysis

### Study design

ElucidatiNg Immunosuppressant pharmacokinetic variabilities by investigating Gut Microbiome modulations After kidney transplantation (ENIGMA) is a single-centre, prospective, low-interventional, naturalistic, longitudinal trial in which 50 living donor kidney transplant recipients are followed for 14 months (European Union Clinical Trial (EUCT) number 2023–5 08 335-31-00). The patients receive standard of care immunosuppressive therapy consisting of TAC (Advagraf), MMF (Cellcept) and corticosteroids. Each patient is enrolled approximately 2 months before kidney transplantation and followed for 12 months post-surgery.

All living kidney donors are managed according to the standard procedures required in the accredited transplant centre and in line with the international guidelines.^42^ Donors are not participants in this clinical trial, and their care is not modified by the study. Before donation, donors undergo a comprehensive medical assessment, as well as informed consent procedures. During the donation procedure, perioperative management follows established institutional protocol for living donor nephrectomy. After donation, donors receive routine postoperative follow-up as recommended by international guidelines, including early postoperative care, monitoring of renal function and long-term follow-up visits.

The trial is designed in three different periods: pre-transplant, hospitalisation and ambulatory period (figure 1). During these visits, a complete biological sampling set including blood, urine and faeces is collected. The different blood collection tubes are Li Heparin LH/7.5 mL (Sarstedt) for proteomic and metabolomic analysis, EDTA K3E/3.4 mL (Sarstedt) for pharmacogenetic testing and immunosuppressants blood concentration measurements, Tempus Blood RNA tubes (Thermo Fisher Scientific) for transcriptomic analysis, BD Vacutainer CPT Mononuclear Cell Preparation Tube – Sodium Heparin (BD Biosciences) for peripheral mononuclear blood cell (PBMC) isolation and Cell-Free DNA BCT (Streck) for donor-derived cell-free DNA analysis. The faecal sample is accompanied by a dietary and medication questionnaire. During the follow-up, a food frequency questionnaire will be carried out twice (once for period before transplantation, once for period post-transplantation).

**Figure 1 F1:**
[figure not shown]
ElucidatiNg Immunosuppressant pharmacokinetic variabilities by investigating Gut Microbiome modulations After kidney transplantation (ENIGMA) longitudinal trial design. D, day; M, month; PBMC, peripheral blood mononuclear cells; PK, pharmacokinetic; SOC, standard of care; µsampling, microsampling.

Concerning the preanalytical treatment of the collected samples, plasma is separated in heparinized tubes after centrifugation (2600 g for 10 min at 4°C). PBMCs are isolated according to manufacturer’s protocol. Cell-free DNA is isolated according to manufacturer’s protocol as well. All samples are aliquoted and snap freezed in liquid nitrogen before storage at −80°C within 2 hours after collection. Faeces are frozen at −20°C immediately after sampling and transferred to −80°C within 3 days after collection. Whole blood for TAC quantification is stored at 4°C before analysis. MPA blood samples are collected on ice in a cold transport container and centrifuged at 871 g for 10 min at 4°C. Plasma is then acidified by addition of orthophosphoric acid 85% (1/50) and stored at −80°C before MPA and metabolite quantification.

Depending on the visit, the composition of the set varies slightly. Stool, urine and blood samples are collected at every visit. The EDTA whole blood sample used for pharmacogenetic testing is collected once at the M-2 visit. PBMCs are collected starting from the D0 visit to study the intracellular concentration of immunosuppressive drugs. A Tempus Blood RNA tube is collected at every other visit post-transplantation. The Cell-free DNA BCT tube is collected once at the M12 visit.

In addition, two types of PK profiling are performed to assess the drug exposure through two different approaches: a full PK curve time course during hospitalisation and a truncated PK curve at different occasions in an ambulatory setting. The full PK curve consists of eight sampling time points in 24 hours (at 0, 1, 2, 3, 6, 8, 12 and 24 hours after TAC intake). MPA is taken 20 min before the first time point (figure 2A). The truncated PK curve consists of three sampling time points (at 0, 35 min and 2 hours and 25 min after TAC intake) (figure 2B). MPA is again taken 20 min before the first time point.

**Figure 2 F2:**
[figure not shown]
(A) Full pharmacokinetic curve scheme. (B) Truncated pharmacokinetic curve scheme. h, hours; min, minutes; MPA, mycophenolic acid; TAC, tacrolimus.

#### Pre-transplant period

Standard pre-transplant visits allow to plan three baseline biological material collection points, 2 months, 1 month and just before transplantation when the patient is hospitalised. During these three visits, a biological sampling set is collected.

#### Hospitalisation period

During the hospitalisation period, samples are collected directly after transplantation (between days 0 and 5) and as from day six after transplantation. The full PK curve is sampled as from day six as well.

#### Ambulatory period

In the standard of care, after discharge of the hospital, the patient visits the hospital regularly. Biological sampling collection takes place at four of these visits, at 1, 3, 6 and 12 months post-transplantation. A truncated PK curve is sampled at each of these four visits.

### Antibiotics

The study also intends to explore the PK of antibiotics usually administered in the management of infections in kidney transplant patients. Its relationship with microbiota modulations and the consequences on immunosuppressive drug PK and clinical outcomes will be tested as well. Therefore, if, for any medical reason (eg, infection), the patient must initiate an antibiotic therapy, and an additional set of biological samples after this medication change is collected. This visit consists of collecting various biological samples (as mentioned in *Study design*) and performing a truncated PK curve.

### Volumetric absorptive microsampling substudy

With the aim to collect complementary PK data, patients are invited to take part in a substudy that involves the drawing of blood samples at home using a volumetric absorptive microsampling device. The same scheme of sampling as for ambulatory visits is scheduled at home (C_0h_-C_35min_-C_2h25_ for TAC corresponding to C_20min_-C_55min_-C_165min_ for MPA). The patient is informed about the possibility to benefit from this follow-up at home during the study inclusion. If he/she agrees to provide microsampling measurements, he/she is trained to use the Mitra Microsampling Device during the hospitalisation period under the supervision of trial staff. Per patient, maximum four truncated PK curves are sampled at home in the 1-year post-transplantation period.

### Study population

The study population will include 50 kidney transplant patients planned for a living-donor kidney transplant. All patients are aged >18 years old and <75 years old with a body mass index ranging from 18 to 35 kg/m^2^. Both ABO-compatible and incompatible situations are considered for inclusion. As inflammatory bowel diseases (IBD) and bariatric surgery are known to be linked to altered microbiota composition and function; no patients suffering from IBD or having undergone bariatric surgery are considered for participation to the study because of the risk of a strong confounding effect. The full list of inclusion and exclusion criteria is available in box 1.

Box 1Full inclusion and exclusion criteria of the ElucidatiNg Immunosuppressant pharmacokinetic variabilities by investigating Gut Microbiome modulations After kidney transplantation (ENIGMA) trialInclusion criteriaDiagnosis of chronic renal failurePlanned for a kidney transplantationReceiving a living-donor kidneyFollowed at Cliniques Universitaires Saint-LucImmunosuppressive treatment consisting in a combination of Tacrolimus (Advagraft) and mycophenolate mofetil (Cellcept)Aged between 18 and 75 years old at time of enrolmentBMI ranging from 18 to 35 kg/m^2^Not being pregnantExclusion criteriaDiagnosis of IBDHistory of bariatric surgeryAlcohol or drug addictionAged<18 or >75 years oldBMI lower than 18 or higher than 35 kg/m^2^ kg/m2PregnancyNot able to provide informed consentBMI, body mass index, IBD, inflammatory bowel disease

#### Primary and secondary outcomes

The primary endpoints are related to immunosuppressive drug (including TAC, MPA and metabolites) and antibiotic PK parameters. These include but will not be limited to drug and metabolite blood exposure as assessed by the trough concentration (C_0h_) or area under the curve (AUC_0-t_) (extrapolated or calculated), drug dosage, PBMC drug concentration and accumulation and drug/metabolite concentrations in faecal material.

Microbiota composition and function are also considered as primary outcomes. This includes diversity estimation and bacterial relative abundance determination as assessed by 16S ribosomal ribonucleic acid (rRNA) gene amplicon sequencing, virome characterisation as assessed by shotgun metagenomics and/or a targeted approach and faecal metabolomic profiling.

Secondary outcomes consist of markers of drug-related toxicity, markers of graft rejection, markers of antibiotherapy efficacy and patient-omic profiling (see table 1 for non-exhaustive specified secondary outcomes).

**Table 1 T1:** Secondary outcomes of the ElucidatiNg Immunosuppressant pharmacokinetic variabilities by investigating Gut Microbiome modulations After kidney transplantation (ENIGMA) trial

Secondary outcomes			
Markers of drug-related toxicity	Markers of graft function and rejection	Markers of antibiotherapy efficacy	Patient -omic profiling
Diabetes mellitus	Creatinine	Resistance	Blood transcriptomics
Hypertension	Glomerular filtration rate	Recurrence	Plasma and urinary metabolomics
Renal toxicity	Graft functional biomarkers		Blood and urinary lipidomics
Diarrhoea and GI toxicity	Per protocol biopsy and histologic anatomopathological evaluation		Plasma proteomics
Neurotoxicity	Circulating donor cell-free DNA measurement		Whole exome sequencing
Infections	Donor-specific antibodies (DSA)		
Tumours			

GI, gastrointestinal.

### Sample size calculation

Power calculation indicates that a sample size of 50 patients with nine repeated PK measurements will provide an 80% statistical power considering a type I (alpha error) of 5% to detect clinically relevant results. The power to detect true associations strongly depends on effect size, heterogeneity of the background noise and sample size. The noise signal is limited by (i) anticipating baseline measurements, (ii) selecting living-donor recipient (limits the variability in phenotypes), (iii) monitoring the individuals over a long period of time (ie, 12 months) and (iv) detaching the interoccasion from the intraoccasion variability.

Considering an SD of 57.5 ng/mL per mg/kg in the TAC dose requirement (preliminary data) and a repeated measurement design with 9 PK time points, a power of 0.8 (1-β = π=80%) can be guaranteed to detect a Δmean as low as 17.25 ng/mL per mg/kg across the levels of a tested-independent variable with a typical type I (α) error of 0.05 (ie, effect size=0.30) which correspond to an average ΔCmin of 2.6 ng/mL considering a typical standard dose (ie, 0.15 mg/kg). This difference can be considered as clinically relevant (therapeutic target 7–20 ng/mL).

Considering a SD of 2.6 µg/mL in the MPA concentrations for a typical dose of 1000 mg (preliminary data) and a repeated measurement design with 9 PK time points, a power of 0.8 (1-β = π=80%) can be guaranteed to detect a Δmean as low as 0.78 µg/mL across the levels of a tested independent variable with a typical type I (α) error of 0.05 (ie, effect size=0.30). Considering that the range of MPA exposure varies between ±2 to 10 µg/mL depending on the time post-dose, this difference can also be considered as clinically relevant.

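### The stated 80% power assumes nine PK measurements in all 50 patients, but only five PK curves are scheduled for every patient; the effect on power is modest

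*Protocol article*

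**What the plan says.** The protocol article, under *Sample size calculation*, claims that "a sample size of 50 patients with nine repeated PK measurements will provide an 80% statistical power" at a type I error of 5%. The TAC and MPA paragraphs each repeat the input as "a repeated measurement design with 9 PK time points, a power of 0.8", and each describes that power as guaranteed. Both use an effect size of 0.30, obtained for TAC as 17.25/57.5 and for MPA as 0.78/2.6.

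The schedule is set out by period:

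- *Pre-transplant period*: "Standard pre-transplant visits allow to plan three baseline biological material collection points". A sampling set is taken at each; no PK curve is described.
- *Hospitalisation period*: one sample collection between days 0 and 5, and another from day 6. "The full PK curve is sampled as from day six as well".
- *Ambulatory period*: visits at months 1, 3, 6 and 12. "A truncated PK curve is sampled at each of these four visits".

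Two other sections can add curves. In *Volumetric absorptive microsampling substudy*, patients are invited to sample at home, and "maximum four truncated PK curves are sampled at home in the 1-year post-transplantation period". In *Antibiotics*, a truncated curve is added if a patient has to start antibiotic treatment.

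**The concern.** The abstract also gives nine as the number of sampling timepoints before and after transplantation together. The likeliest explanation is that this visit count was carried into the power statement as a count of PK measurements. The article does not say which nine are meant.

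The number of repeats per patient is a direct input to a repeated-measures power calculation. This section is the article's only quantitative justification for 50 patients. If the input is larger than what every patient is scheduled to provide, the stated power belongs to a fuller data set than the core schedule yields.

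**Working it through.** **Step 1: count the occasions.**

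| Period | Sampling visits | Scheduled PK curves |
|---|---|---|
| Pre-transplant | 3 | 0 |
| Days 0–5 | 1 | 0 |
| From day 6 | 1 | 1 (full) |
| Months 1, 3, 6, 12 | 4 | 4 (truncated) |
| Total | 9 | 5 |

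A patient who volunteers for the home substudy and completes the maximum reaches 5 + 4 = 9. Draws within one curve do not explain the nine: the full curve has eight and the truncated curve three.

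**Step 2: reproduce the stated 80%.**

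Inputs from the article: N = 50, m = 9, alpha = 0.05, effect size 0.30. Inputs assumed because the article does not give them: a between-patient factor with k = 2 levels, a within-patient correlation rho = 0.5, and 0.30 read as Cohen's f.

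The test is a repeated-measures F test with k − 1 = 1 and N − k = 48 degrees of freedom (critical value 4.04) and noncentrality

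lambda = f² × N × m / (1 + (m − 1) × rho).

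For m = 9: lambda = 0.09 × 50 × 9/(1 + 8 × 0.5) = 4.5 × 1.8 = 8.10, and power = 0.796. This matches the stated 80%; reaching 0.80 exactly would take 51 patients.

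Reading 0.30 as Cohen's f is itself an assumption. The article forms it as a mean difference over an SD, which for two equal groups would be f = 0.15. The same formula then gives 0.286 with nine occasions, which does not reproduce the claim. That is a separate question; Cohen's f is used here because it recovers the article's figure.

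**Step 3: change only the number of occasions (rho = 0.5).**

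- m = 5: lambda = 4.5 × 5/3 = 7.50; power 0.765; 55 patients needed for 80%.
- m = 6, if a concentration from days 0–5 is counted: lambda = 4.5 × 6/3.5 = 7.71; power 0.777.
- Smallest f detectable with 80% power at N = 50: 0.301 with nine occasions, 0.313 with five.

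**Step 4: vary the correlation.**

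| rho | m = 9 | m = 5 | Loss |
|---|---|---|---|
| 0.3 | 0.922 | 0.880 | 0.043 |
| 0.4 | 0.861 | 0.822 | 0.039 |
| 0.5 | 0.796 | 0.765 | 0.031 |
| 0.6 | 0.735 | 0.713 | 0.023 |
| 0.7 | 0.680 | 0.664 | 0.016 |

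Losses are taken before rounding. With five occasions power crosses 0.80 at rho = 0.438; at rho = 0.43 it is 0.805.

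**Step 5: partial uptake of home sampling (rho = 0.5).** If 25%, 50% or 75% of patients gave all four home curves and the rest gave five in total, power would be 0.773, 0.781 or 0.789.

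**The case against.** The strongest reply is that a PK measurement need not be a full or truncated curve. The TAC effect is translated into a difference in minimum concentration, trough concentration is a listed exposure measure, blood is drawn at every visit, and TAC is monitored routinely. This has some force: a day 0–5 concentration could make six, and routine troughs could add more for TAC. It does not explain nine for both drugs. The pre-transplant visits have no described drug measurement, and the article says monitoring is not routine for MMF.

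A second reply is that five scheduled plus four home curves make exactly nine, on the same sampling scheme as the ambulatory visits. That is correct, and it rules out saying that the trial has no route to nine. But home sampling is voluntary, four is a maximum, and the article presents the data as complementary. It cannot support a power figure claimed for all 50 patients. Antibiotic visits depend on events.

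A reader might also infer several stronger things that the documents do not support:

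- **That the stated 80% is missed.** This depends on a correlation, a number of levels and a reading of 0.30 that the article does not give.
- **That power is far lower after withdrawals or with a three-level factor.** Most of such a fall would come from the smaller N or the extra level, which lower power with nine occasions too. The article also keeps data collected before withdrawal, with stated exceptions.
- **That within-patient analyses are badly weakened.** The 80% is recovered for a between-patient factor. Under the same assumptions a within-patient factor has power above 0.99, so a loss there does not show that the stated figure fails. The variability index uses dose-adjusted concentrations over follow-up, which need not be limited to the five curves.

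**Conclusion.** The inconsistency stands. The power statement uses nine PK measurements in every patient, whereas the schedule common to all patients has five PK curves, and nothing in the article assures the other four. The consequence is modest: about 3 points at a correlation of 0.5, and about 2 to 4 points between 0.3 and 0.7. These figures rest on a two-level between-patient factor, 50 patients, alpha 0.05 and 0.30 taken as Cohen's f. Whether five occasions fall short of 80% is not settled by the documents, because it turns on a correlation that they do not state. The point concerns a design input and the figure derived from it. It does not show that the trial is unable to answer its question.

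**What to change.** Recompute and restate the power, or the detectable difference at 80% power, for TAC and for MPA with the five PK occasions scheduled for all patients. State the within-patient correlation and the number of levels of the tested variable, preferably with a short range for the correlation. Leave the voluntary home curves out of the powered count. Correct all three statements of nine in *Sample size calculation*: the opening sentence and the TAC and MPA paragraphs. If a day 0–5 concentration is meant to count, say so and use six.

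The cost is one rerun of the calculation and a few sentences. No visit, sample, endpoint or analysis changes. The restated power may come out a few points lower, or the detectable difference slightly larger.
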